### Randomisation

Participants will be randomly allocated in a 1:1 ratio to either intervention or control group arms. Randomisation will be stratified by investigator site and baseline pro-brain natriuretic peptide (NT pro-BNP) levels (≤2000, >2000 pg/mL) using minimisation to facilitate balance between the two treatment arms. Randomisation numbers will be computer generated and assigned in strict sequence. At the point of randomisation, participants will be assigned the next randomisation number in the sequence. To maintain concealment and minimise selection bias, randomisation will be performed after the baseline visit by a member of Peninsula Clinical Trials Unit (CTU), independent from investigator teams, using a secure, web-based randomisation system.

### Intervention

The REACH-HF intervention is grounded in the support needs and priorities of people living with HF and the services that provide care for them. A systematic, six-step Intervention Mapping framework^13^ guided intervention development, drawing on research evidence, national and international guidelines and stakeholder consultations with patients, caregivers and health professionals to identify ‘targets for change’. In line with Intervention Mapping regulatory processes, underpinning target behaviour patterns and evidence-based change techniques were matched to each behaviour-change target.^14^ A key element of the intervention development process was an active Patient and Public Involvement group consisting of six people with a range of experiences with HF and three caregivers of people with HF. The intervention development process is described in detail elsewhere ([name], [name], [name], *et al*. Development of a facilitated self-care and rehabilitation intervention for people with HF and their care givers: Rehabilitation Enablement in Chronic Heart Failure (REACH-HF). Submitted for publication 2015).

The REACH-HF intervention is a comprehensive self-care support programme comprising the ‘Heart Failure Manual’ (HF Manual), with a choice of two exercise programmes for patients, a ‘Family and Friends Resource’ for caregivers, a ‘Progress Tracker’ tool and a training course for intervention facilitators.

Participating patients and caregivers will work through the self-help manual over a 12-week period with facilitation by a specially trained intervention facilitator (cardiac nurse or physiotherapist by background), who will help to build the patient's and caregiver's understanding of how to manage HF. The manual includes information and interactive elements covering a wide range of topics relating to living with/adapting to living with HF, and includes four core elements:
An exercise training programme, tailored according to initial fitness assessments, delivered as a walking programme or a chair-based exercise DVD, or a combination of the two (the patient's choice);Managing stress /breathlessness /anxiety;HF symptom monitoring (and associated help-seeking);Understanding and taking medications.

Patients will be encouraged to use the progress tracker booklet, which is designed to collect the following information over the period of the intervention: changes in physical and mental state, intensity of exercise and self-reported walking speed, and degree of completion of self-monitoring sections for physical activity, enjoyable activities, frequency of self-weighing (to monitor fluid build-up), and frequency of self-reported use of stress-management techniques. The Family and Friends resource, a manual for use by caregivers, includes advice on providing support, becoming a caregiver, managing caregiver's own health and well-being and getting help.

As a pragmatic trial of a self-help intervention which is reliant on the willing engagement of recipients, there are no specific strategies to improve participants’ adherence to intervention protocol. Intervention delivery may be discontinued at any time at the request of a participant or by the intervention facilitator if they determine that the intervention may be the cause of undue harm.

Adherence to intervention protocols from the perspective of the intervention facilitators will be ascertained through fidelity assessment described herein.

### Usual care

In accord with findings of our national survey,^9^ patients with HF typically do not receive CR, despite NICE recommendations.^1^ The choice of a usual care (no rehabilitation) comparator in the REACH-HF trial is therefore reflective of the situation for the vast majority of patients with HF. In this trial, intervention and control group patients will receive usual medical management for HF according to national and local guidelines, including specialist HF nurse care. The use of care services, including those provided by specialist HF nurses in the community and in secondary care, will be documented at each follow-up through participants’ completion of healthcare resource use questionnaires and by collection of concomitant medication usage as reported by participants.

### Outcome measures

Outcome data will be collected at 4, 6 and 12 months following the baseline visit (table 1—Tabulated summary of study schedule). The 4-month time point coincides with the end of the 3-month intervention delivery period for participants in the intervention arm. This allows a 1 month period after the baseline visit for completion of randomisation and referral processes.

**Table 1 BMJOPEN2015009994TB1:** Tabulated summary of study schedule

[figure not shown]

*Six month time point is conducted by post. Participants are not required to visit the research centre at this time point.

†Allocation will be performed by Peninsula Clinical Trials Unit (CTU), typically within 10 days of the baseline clinic, following receipt of baseline data and blood sample result.

‡HF Manual f*a*cilitation will commence approximately 1 month post randomisation.

HADS, Hospital Anxiety and Depression Scale questionnaire; HF, heart failure; MLHFQ, Minnesota Living with HF questionnaire; pro-BNP, pro-brain natriuretic peptide; QoL, quality of life; SCHFI, Self-care of HF Index questionnaire; CC-SCHFI, Caregiver Contribution to Self-care of HF Index questionnaire; CBQ-HF, The Caregiver Burden Questionnaire for HF; FAMQOL, Family Caregiver QoL questionnaire.

#### Primary outcome

Patient disease-specific HRQoL measured using the Minnesota Living with HF questionnaire (MLHFQ) at 12 months. The questionnaire consists of 21 items and is designed to represent the ways HF and treatments can affect the key physical, emotional, social and mental dimensions of an individual's quality of life.^15^

#### Secondary outcomes

##### Patients

Composite outcome of death or hospital admission related to HF or not related to HF. All instances of hospitalisation and death will be recorded and made accessible to an independent adjudication panel of three experienced cardiologists who will ascertain whether or not reported events are HF-related.NT pro-BNP levels. Natriuretic peptide levels are elevated in patients with HF.^16^Exercise capacity (incremental shuttle walk test (ISWT)).^17^Physical activity level (accelerometry over a 7-day period, measured using the GENEActiv Original accelerometer).^18^Psychological well-being using Hospital Anxiety and Depression Scale questionnaire (HADS).^19^Generic HRQoL using the EQ-5D-5L questionnaire.^20^Disease-specific quality of life using the Health-related Quality of Life (HeartQoL) questionnaire.^21^Self-care of HF Index questionnaire (SCHFI).^22^Healthcare utilisation (ie, primary and secondary care contacts, social care contacts and relevant medication usage).Self-efficacy for key behaviours questionnaires (developed by the research team).Safety; recording and reporting of serious adverse events. Any adverse event or adverse reaction will be regarded as serious if it: results in death, is life-threatening, requires hospitalisation or prolongation of existing hospitalisation, results in persistent or significant disability or incapacity. All serious adverse events that occur during the trial will be recorded and reported to the Ethics Committee, the Data Monitoring Committee and the Trial Steering Committee.

##### Caregivers

Psychological well-being using the HADS.^19^Generic HRQoL using the EQ-5D-5L questionnaire.^20^Caregiver Contribution to Self-care of HF Index questionnaire (CC-SCHFI).^22^Caregiver Burden Questionnaire—HF.^23^Family Caregiver Quality of Life Scale questionnaire (FAMQOL).^24^

### Sample size

The sample size is based on an effect size that represents a clinically important difference and is plausible. The developers of the MLHFQ have determined that five points is the minimal clinically important difference in score.^15^ With a type I error of 0.05 and power of 90%, 85 patients per group are required to detect a five-point difference in the MLHFQ score, assuming a SD of 10.^25^ With an attrition rate of 20% (in accordance with the level of attrition seen in previous trials),^26^
^27^ 108 patients are required per group. The plausibility of this between group difference is supported by the Cochrane review of CR in HF, which reported a mean pooled between group difference of 10.3 (95% CI 4.8 to 15.9) points in MLHFQ score.^28^ The proposed sample size is likely to be conservative given the analysis of covariance approach to primary outcome analysis and adequate to detect an important difference in a number of secondary outcomes, including the ISWT (50 m) and Hospital Anxiety and Depression Scale (1.5 points) at a power of 80% or higher.

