#### Process evaluation study 1: Intervention fidelity

A fidelity checklist developed and piloted as part of the REACH-HF programme ([name], *et al* Submitted for publication 2015) will be used to assess fidelity of delivery of the intended intervention processes. This will be achieved by analysing recordings of all contacts (telephone and face to face) between intervention facilitators and 20 purposively sampled patient participants. Contacts will be audio recorded by intervention facilitators and the files made accessible to two researchers who were part of the REACH-HF intervention development team (a chartered health psychologist and a registered nurse (by background)) who will complete the checklist while listening to the recordings. The check list is based on the Dreyfus scale.^30^ This will clarify how well (or otherwise) intervention components are delivered and received and will also allow researchers to describe variability in fidelity of delivery across patients and facilitators.

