### Data analysis

#### Primary and secondary outcomes

All analyses, quantitative and qualitative, will be conducted according to best practise and reported in accordance with Consolidated Standards of Reporting Trials (CONSORT) guidelines for reporting of clinical trials^31^ and appropriate guidelines for reporting process evaluations^32^ and qualitative research.^33^ Baseline sociodemographic and health-related variables will be reported descriptively by treatment arm, in order to assess whether the inferential analyses require adjustment for any unbalanced variables.

The primary analyses for all patient and caregiver outcomes will be based on a between-group, intention-to-treat, complete case approach, using data collected at 12 months’ follow-up. The outcomes will be analysed using the regression method appropriate to the data, that is, linear regression modelling for continuous outcomes, survival analysis based on the Cox proportional hazards regression model for time-to-event data, and Tobit regression analysis for EQ-5D-5L. All analyses will adjust for baseline score of the outcome variable (where applicable), as well as minimisation variables previously described, and sociodemographic and health-related variables that are found to be unbalanced at baseline.

Secondary analyses will be undertaken on patient and caregiver outcomes as repeated measures analysis using all follow-up assessment points (4, 6 and 12 months). In addition, a per protocol analysis of the primary outcome will be performed using 12-month follow-up data. A per protocol definition (based on a minimum level of intervention uptake and adherence deemed necessary to achieve improvement in outcomes) will be agreed prior to the start of data analysis. If there is more than 5% loss to follow-up for the primary outcome at 12 months, multiple imputation methods will be used as a sensitivity analysis to address the issue of missing data. The following subgroups will be assessed: the stratification variables of trial centre and severity of HF (NT pro-BNP levels), plus time since HF diagnosis and the inclusion (or not) of a caregiver.

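### Facilitator clustering in the intervention arm is left out of both the stated primary model and the claim that the sample size is conservative, so that claim is unsupported and the primary interval is too narrow if facilitators differ

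*Protocol article*

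**What the plan says.** Under Intervention, intervention patients work through the manual over 12 weeks "with facilitation by a specially trained intervention facilitator". Under Usual care, controls receive usual management without this support. Process evaluation study 1 will use a checklist that lets researchers "describe variability in fidelity of delivery across patients and facilitators".

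The Sample size section treats patients as independent: "With a type I error of 0.05 and power of 90%, 85 patients per group are required", a number "required to detect a five-point difference in the MLHFQ score, assuming a SD of 10". It then allows for loss to follow-up ("With an attrition rate of 20% (in accordance with the level of attrition seen in previous trials") and concludes that "108 patients are required per group". It adds: "The proposed sample size is likely to be conservative given the analysis of covariance approach to primary outcome analysis". It gives no ICC, facilitator number or design effect.

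Under Data analysis, Primary and secondary outcomes, the method is "linear regression modelling for continuous outcomes", adjusted for the baseline score, the minimisation variables (site and NT pro-BNP group) and covariates found unbalanced at baseline. Facilitator does not appear in the model.

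**The concern.** Patients who share a facilitator share whatever that person does well or badly. Their outcomes may then be positively correlated, while control outcomes are not. This is a partially nested design. A regression that treats all patients as independent understates the variance of the intervention mean, and with it the standard error of the treatment difference.

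Two statements in the protocol are affected:

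- **The primary model.** If facilitators differ, the primary confidence interval covers less than 95% and the test rejects a true null more than 5% of the time.
- **The claim about sample size.** Baseline adjustment reduces the variance and clustering increases it. Calling the size conservative on the first alone settles the direction of the net effect without looking at the second.

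**Working it through.** **Step 1. Reproduce the stated figures.** Inputs from Sample size: difference 5, SD 10, type I error 0.05 (taken as two-sided), power 90%, attrition 20%.

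n = 2 × (1.960 + 1.2816)² × (10/5)² = 84.06, so 85 per group. The t-test power at 85 is 90.0%. Then 85/0.8 = 106.3, so 107, and 86/0.8 = 107.5, so 108. Conversely, 108 × 0.8 = 86.4, so about 86 analysed per arm, with t-test power 90.3%. The figures 85 and 108 reproduce under independence.

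**Step 2. Add clustering in the intervention arm.** The document gives no facilitator number k, ICC or baseline-to-12-month correlation r. I assume k = 4, 8, 12 (four sites are stated), ICC = 0.01, 0.02, 0.05, and r = 0 or 0.5. With n = 86 and m = 86/k:

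- Design effect, intervention arm: DE = 1 + (m − 1) × ICC
- Variance ratio, true to naive, at r = 0: V = (DE + 1)/2
- Naive type I error: 2 × [1 − Φ(1.96/√V)]
- Variance of the difference: 100 × [2(1 − r²) + (m − 1) × ICC]/86
- Power: Φ(5/SE − 1.96)

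The variance formula defines the ICC on the unadjusted scale: baseline adjustment removes patient variation, but facilitator effects arise after randomisation and remain.

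Example, k = 8, ICC 0.05: m = 10.75, DE = 1 + 9.75 × 0.05 = 1.4875, V = 1.244. Naive type I error is 2 × [1 − Φ(1.757)] = 7.9%. At r = 0, SE = 10 × √(2.4875/86) = 1.701 and power is Φ(2.940 − 1.96) = 84%. At r = 0.5, SE = 10 × √(1.9875/86) = 1.520 and power is Φ(3.289 − 1.96) = 91%.

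| k | ICC | V | SE ratio √V | Naive type I error | Power, r = 0 | Power, r = 0.5 |
|---|---|---|---|---|---|---|
| 4 | 0.01 | 1.10 | 1.05 | 6.2% | 88% | 94% |
| 4 | 0.02 | 1.21 | 1.10 | 7.4% | 85% | 92% |
| 4 | 0.05 | 1.51 | 1.23 | 11.1% | 76% | 83% |
| 8 | 0.01 | 1.05 | 1.02 | 5.6% | 89% | 96% |
| 8 | 0.02 | 1.10 | 1.05 | 6.1% | 88% | 95% |
| 8 | 0.05 | 1.24 | 1.12 | 7.9% | 84% | 91% |
| 12 | 0.01 | 1.03 | 1.02 | 5.4% | 90% | 96% |
| 12 | 0.02 | 1.06 | 1.03 | 5.7% | 89% | 95% |
| 12 | 0.05 | 1.15 | 1.07 | 6.8% | 86% | 93% |

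Power here is for a test that uses the correct variance, by normal approximation. Small-sample degrees of freedom would lower it somewhat when k is small.

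If the ICC is instead defined after baseline adjustment, the whole variance scales by 1 − r². Power at r = 0.5 is then slightly higher (87% for k = 4 and 92% for k = 8, both at ICC 0.05), and type I error is unchanged from the table.

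**Step 3. Does adjustment cure the type I error?** No. On the unadjusted scale it makes the relative error larger, because the naive variance shrinks and the facilitator part does not: at k = 4, ICC 0.05, r = 0.5 the naive type I error is about 13%. Site as a main effect does not help either. Facilitator effects occur in one arm only, so the treatment difference within each site still carries them in full. A simulation of the protocol's type of model (84 per arm, four site effects, baseline covariate, facilitators nested in site, ICC 0.05, 40,000 runs) gave these rejection rates under the null:

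| k | r = 0 | r = 0.5 |
|---|---|---|
| 4 | 11.2% | 13.1% |
| 8 | 7.9% | 8.8% |
| 12 | 6.7% | 7.1% |

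**Step 4. When does baseline adjustment offset the power loss?** When r² = (m − 1) × ICC/2. This runs from r = 0.18 (k = 12, ICC 0.01: 6.17 × 0.01/2 = 0.031) to r = 0.72 (k = 4, ICC 0.05: 20.5 × 0.05/2 = 0.51).

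**The case against.** The strongest reply is that the protocol's claim may be true. With r = 0.5, 8 facilitators and ICC 0.05, power is still about 91%, and with 12 facilitators about 93%. That stands. A reader might infer that the 90% power is overstated, or that the standard errors are certainly wrong. The document supports neither, because it gives no ICC, facilitator number or baseline correlation. Planning to describe variability in delivery is also not evidence that 12-month MLHFQ scores correlate within facilitator. The intervention is self-help, and the outcome is measured months after facilitation ends, so the ICC could be small.

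A reader might also infer that the SD of 10 is already an adjusted or change-score SD, so that the gain from baseline adjustment is counted twice. The text describes it only as an SD in connection with the MLHFQ score and cites a source not at hand. That inference has no support here.

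A third reply is that random-effect structure belongs in the analysis plan, which is not shown. This has force for fine detail. But the protocol itself states the model and makes a positive claim about the direction of error in its sample size, so both can be judged as written.

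None of these replies rescues the type I error: a gain in precision from baseline adjustment does not make an independence-based standard error valid under clustering.

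**Conclusion.** The concern holds in conditional form. If facilitators differ at all, the stated model gives a primary confidence interval that is too narrow and a p-value that is too small, and neither baseline nor site adjustment corrects this. Over the assumed range (4 to 12 facilitators, ICC 0.01 to 0.05) the true standard error is about 2% to 23% larger than the naive one at r = 0, and naive type I error is about 5.4% to 11%.

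For power, the conservative claim is unsupported rather than shown to be false. With 86 analysed per arm and SD 10, power is about 76% to 90% at r = 0 and 83% to 96% at r = 0.5. The stated 85 and 108 are correct under their own assumptions.

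**What to change.** 1. Pre-specify for the primary outcome a partially nested mixed model: facilitator random effect in the intervention arm only, controls as singletons, arm-specific residual variance and small-sample degrees of freedom. At a minimum, make it a sensitivity analysis reported beside the main result.
2. Fit it after the blinded primary analysis. The protocol has a statistician blinded to allocation, and a facilitator term reveals arm.
3. Record facilitator identity for each intervention patient. The participant-level facilitator time forms described under Economic evaluation are a natural place; the protocol does not say whether they already capture it.
4. In Sample size, replace the conservative claim with a statement along these lines: 90% power assumes an SD of 10 and no facilitator clustering; baseline adjustment may or may not offset clustering; power is shown over stated ranges of ICC, facilitator number and baseline correlation.

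Patient numbers do not change. The cost is some added text, one data field and one further model. The downsides are a slightly wider confidence interval and, if facilitators are few, an imprecisely estimated variance component.

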### Trial data collection

Trial data are collected from participants during three clinic visits (at baseline, 4 and 12 months) and by postal questionnaire at 6 months. To encourage participant retention and completeness of data, participants may claim travel expenses associated with clinic visits and are provided with postage-paid envelopes to return questionnaires by post. Furthermore, visits may be partially conducted at participants’ homes if mutually convenient for the research nurse and participant. Participants who are unwilling or unable to travel to research assessments or accommodate home visits are excluded at the point of consent.

At the baseline clinic visit, after written informed consent has been obtained by the research nurse, the following information will be collected:
Medical history (including comorbidities (number and severity scored with Charlson Co-morbidity Index), New York Heart Association class, HF aetiology, concomitant HF medication and presence of implantable HF devices);Healthcare resource utilisation over the prior 6 months;Sociodemographic information (ie, date of birth, ethnicity, height, weight, employment status, education level, smoking status).

Participating patients will be asked to:
Complete a booklet comprising the primary and secondary outcome questionnaires;Perform an the incremental shuttle walk test;Provide a (∼4 mL) blood sample for measurement of NT pro-BNP levels;Wear a wrist-worn accelerometer for 7 days.

Participating caregivers will also be asked to provide sociodemographic information (ie, date of birth, ethnicity, weight, employment status, education level and smoking status) and to complete a booklet comprising their outcome questionnaires.

Patient and caregiver follow-up outcome assessments will be performed at clinic visits held at 4 and 12 months after the baseline visit, with a postal follow-up (questionnaire-based outcomes only) performed at the 6-month time point. At the 4 and 12-month clinic visits investigators will record details of any changes to participants’ HF medication or implantable cardiac devices, details of any hospitalisations and healthcare resource utilisation since the previous visit. Investigators will also check that participating patients have not become contraindicated to exercise testing before conducting the incremental shuttle walk test. Blood samples (collected at baseline and 12 months only) will be dispatched to a central laboratory (Royal Cornwall Hospital NHS Trust) for determination of NT pro-BNP levels. Accelerometer devices will be returned by participants using postage-paid envelopes after 7 days of wearing. The devices will be returned to the CTU for data extraction. Participant safety will be monitored through recording, reporting and review of all serious adverse events collected from baseline until final follow-up visit.

Data collected at clinic visits will be recorded on study specific case report forms (CRFs) by the research team at each site. Completed CRFs will be checked and signed at the research sites by a member of the research team before being sent to the CTU. Original CRF pages and completed questionnaire booklets will be posted to the CTU at agreed time points for double-data entry in to the study database. Accelerometer data will be imported directly into the study database. All forms and data will be tracked using a web-based trial management system. Double-entered data will be compared for discrepancies according to a data management plan held in CTU. Discrepant data will be verified using the original paper data sheets.

Participant names and addresses will be collected for the purpose of managing questionnaire dispatch, intervention delivery and participant interviews. Investigators will ensure that the participants’ anonymity is maintained on all other documents. Within the CTU, anonymised and identifiable study data will be stored separately, to prevent the identification of participants from research records, in locked filing cabinets within a locked office. Electronic records will be stored by the CTU in a web-based, SQL server database, housed on a restricted access, secure server maintained by the University of Plymouth. Data in the database will be backed up daily. The website will be encrypted using SSL. Data will be collected and stored in accordance with the Data Protection Act 1998. Direct access to the trial data will be restricted to members of the research team and the CTU, with access granted to the Sponsor on request. Access to the database will be overseen by the CTU data manager and trial manager.

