Early phase after acute coronary syndrome (up to 2 days)Untreated life-threatening cardiac arrhythmiasAcute HF (during the initial period of haemodynamic instability)Uncontrolled hypertension (systolic blood pressure >200 and/or diastolic blood pressure >100)Advanced atrioventricular blockAcute myocarditis and pericarditisSymptomatic aortic stenosisSevere hypertrophic obstructive cardiomyopathyAcute systemic illnessIntracardiac thrombusProgressive worsening of exercise tolerance or dyspnoea at rest over previous 3–5 daysSignificant ischaemia during low-intensity exercise (<2 Metabolic equivalents, <50 Watts)Uncontrolled diabetes (blood glucose >16 mmol/L or glycated hemoglobin >9% or equivalent unit)Recent embolismThrombophlebitisNew-onset atrial fibrillation/atrial flutterPatients who are in a long term care establishment or who are unwilling or unable to travel to research assessments or accommodate home visits.Patients who are unable to understand the study information or unable to complete the outcome questionnaires.Patients judged to be unable to participate in the study for any other reason (eg, psychiatric disorder, diagnosis of dementia, life threatening co-morbidity)Patients participating in concurrent interventional research which may over-burden the patient or confound data collection.

Participating caregivers will be aged 18 years or older and provide unpaid support to patients who could otherwise not manage without such support. Unpaid support includes emotional support, prompting with taking medications, observing for signs and symptoms of HF, getting prescriptions, encouraging participation in social events and physical activity, helping with household tasks or providing physical care.

A patient may still participate if s/he does not have an identified caregiver, or if the patient's caregiver is not willing to participate. Similarly patients who are unable or not willing to undertake the exercise capacity assessment will not be excluded.

Participants are free to withdraw from the study at any time, and this will be emphasised during the consent process. If a participant chooses to withdraw they will be asked to provide a reason and the reason for withdrawal will be noted. Participants do not have to provide a reason and this will be reiterated by the PI (or authorised delegate) in the event of a withdrawal request. Data collected on participants prior to withdrawal will be retained for analysis.

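### The 12-month ISWT analysis drops patients who could not be walk-tested, and the only stated missing-data remedy is triggered by loss on the MLHFQ, not on the ISWT

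*Protocol article*

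**What the plan says.** All places are in the protocol article.

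- **Trial data collection.** At the 4- and 12-month clinics, investigators "check that participating patients have not become contraindicated to exercise testing before conducting the incremental shuttle walk test". The 6-month contact is postal and has no walk test.
- **Study population.** The Box 1 contraindications include acute heart failure and progressively worsening exercise tolerance or breathlessness at rest. They also include conditions such as uncontrolled diabetes, thrombophlebitis and recent embolism. The same section says that "patients who are unable or not willing to undertake the exercise capacity assessment will not be excluded".
- **Data analysis, Primary and secondary outcomes.** The primary analysis of all patient and caregiver outcomes is intention-to-treat, complete case, at 12 months, with linear regression for continuous outcomes. "All analyses will adjust for baseline score of the outcome variable (where applicable"), together with the minimisation variables. Multiple imputation is a sensitivity analysis that comes into play when loss on the primary outcome exceeds 5%. A secondary repeated-measures analysis uses all follow-up points.
- **Sample size.** The planned number is described as "adequate to detect an important difference in a number of secondary outcomes, including the ISWT (50 m") at 80% power or more. No ISWT standard deviation, completion rate or baseline correlation is given.

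**The concern.** Most missing data in this trial will come from patients who do not return. The ISWT has a second source: patients who attend, complete the questionnaires and give blood, but are not walked because of their clinical state. Where that state is worsening heart failure, the value is missing for a reason closely tied to the quantity being measured.

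Complete-case regression then compares the arms among patients fit enough to be tested at 12 months, a group formed after randomisation. If the programme alters how many patients become untestable, the two tested groups are no longer comparable. The stated remedy does not respond, because its trigger looks at the MLHFQ, a questionnaire that needs no exercise.

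At stake is the trial's measure of exercise capacity, which is named individually in the power statement and is a candidate mediator in the process evaluation.

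**Working it through.** **1. The plan's own figure.** Sample size states: "With a type I error of 0.05 and power of 90%, 85 patients per group are required". The other inputs given there are a target of 5 MLHFQ points and an SD of 10. Taking the test as two-sided:

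n = 2 × (1.960 + 1.282)² × 10² / 5² = 84.1, so 85 per group, as stated.

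For 20% attrition, 85/0.8 gives 107. The t-test version needs 85.03, so 86, and 86/0.8 = 107.5, so 108 as stated. The main sample size reproduces.

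**2. What happens to a patient who is not walked.** I assume that the follow-up check uses the Box 1 list.

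| Situation | 12-month complete-case ISWT analysis | Stated remedy |
|---|---|---|
| Attends at 12 months, contraindicated, MLHFQ completed | Drops out | None, unless MLHFQ loss exceeds 5% |
| Walked at 12 months, no baseline test | Drops out if the baseline score is in the model | None stated |
| Walked at 4 months, contraindicated at 12 | Drops out; contributes 4-month data to the repeated-measures analysis | That analysis, which in its usual form assumes missing at random |

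The first and third rows are selection after randomisation. The second row precedes randomisation, so it costs precision but does not unbalance the arms.

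**3. Could this matter? An illustration with assumed inputs.** Baseline mean 300 m, SD 116 m, baseline correlation 0.7, true effect 50 m, baseline-adjusted regression on tested patients only.

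*Loss fixed separately in each arm, patients with the worst change untested:*

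| Untested, control / intervention | Estimated difference |
|---|---|
| 10% / 10% | about 50 m |
| 20% / 20% | about 50 m |
| 20% / 10% | about 38 m |
| 10% / 20% | about 63 m |

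Equal loss leaves the difference almost unchanged. Unequal loss moves it in either direction.

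*One threshold applied to both arms.* The SD of change is 116 × √(2 × (1 − 0.7)) = 89.9 m. If 10% of controls fall below the threshold on change, the intervention share is Φ(−1.282 − 50/89.9) = 3.3%. The arms then differ without any imbalance being put in by hand.

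| Controls untested | Intervention untested (change threshold) | Estimate, threshold on change | Estimate, threshold on 12-month distance |
|---|---|---|---|
| 10% | 3% | about 41 m | about 44 m |
| 15% | 6% | about 38 m | about 41 m |
| 20% | 8% | about 35 m | about 39 m |

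Under these assumptions a true 50 m is understated by about 6 to 15 m. With a true effect of zero, the common threshold produces no bias.

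**4. ISWT power.** The largest SD giving 80% power for 50 m with 85 per group, unadjusted, is

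SD = 50 / (2.80 × √(2/85)) = about 116 m.

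Power = Φ(50/(SD_e × √(2/n)) − 1.96), where n is 85 less the extra loss and SD_e = SD × √(1 − r²) when the baseline is adjusted for at correlation r:

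| Assumed SD, r | No extra loss | 10% | 20% | 30% |
|---|---|---|---|---|
| 100 m, unadjusted | 90% | 87% | 83% | 78% |
| 116 m, unadjusted | 80% | 76% | 71% | 65% |
| 116 m, r = 0.5 | 90% | 87% | 83% | 77–78% |
| 116 m, r = 0.7 | 98% | 96% | 94% | 91% |
| 130 m, unadjusted | 71% | 66% | 61% | 56% |

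The claim of 80% or more can be neither confirmed nor refuted from the document.

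**The case against.** **The safety check and the inclusive entry rule are not errors.** This stands. Neither contradicts anything, and the weakness lies in the analysis rule that meets them.

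**Reason codes and sensitivity analyses belong in the case report forms and analysis plan, which are not shown.** This stands in part. Their absence from an article is not a finding. The article does, however, fix complete case for all outcomes and ties imputation to the primary outcome. Those are stated rules.

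**The worst deteriorations need not be the ones removed.** A reader might infer that untested patients are those who declined most and are known to walk poorly. The documents do not support this: several contraindications are transient or unrelated to walking ability, and no rate is given. Only some of this missingness is plausibly informative.

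**Bias requires unequal loss.** This is correct, and the direction cannot be known in advance. Section 3 of the working shows that a shared clinical threshold can produce unequal loss when the treatment has an effect, but real contraindications are not a clean threshold.

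**Harm would still be visible.** This largely stands. The same attenders can contribute MLHFQ, HADS, NT-proBNP, accelerometry, adjudicated events and serious adverse events. The mediation analysis is declared exploratory.

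**A reader might infer that the stated ISWT power is not delivered.** The documents do not show this. The 116 m SD is the value at which unadjusted power is exactly 80%, so any further loss must fall short of it. The 85 per group is already net of 20% attrition, and baseline adjustment adds power.

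**Conclusion.** The point holds as a weakness of the stated analysis rule for a secondary outcome. ISWT missingness can be informative and can differ by arm while MLHFQ completeness stays high enough that the only stated remedy is never triggered. Even if it were triggered, the text does not say that imputation would extend to the ISWT, and standard imputation assumes missing at random, which is doubtful for a patient untested because of worsening.

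The size and direction of any bias cannot be derived from the documents. The estimate of about 35 to 44 m for a true 50 m rests on an assumed SD, correlation, threshold rule and 10% to 20% of controls being untested; it shows what is possible and is not a forecast. The MLHFQ conclusion is untouched. On power, the supportable remark is limited: the ISWT claim rests on one overall attrition allowance and an unstated SD, so it cannot be checked.

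**What to change.** Amend the Data analysis section and leave the contraindication check as it is.

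1. Record at baseline, 4 and 12 months why each ISWT was not done (heart failure worsening or physical inability; other contraindication; declined; logistical) and report the reasons by arm.
2. Tie the missing-data sensitivity analysis to each outcome's own missingness, not to loss on the MLHFQ.
3. Pre-specify one ISWT sensitivity analysis giving a worst rank or a low value only to patients untested because of heart failure worsening or physical inability, shown beside the observed-walker result. Treat contraindications unrelated to walking ability as ordinary missing data. Giving 0 m to every contraindicated patient would not be sound.
4. Keep patients with no baseline ISWT by a missing-baseline indicator or mean imputation of the baseline.
5. In Sample size, say that the 80% ISWT power allows only for 20% overall attrition, and state the SD and number tested that it assumes.

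The cost is one data field and one extra analysis. The low value is a convention, which is why both results should be shown. Reasons not captured at the visit may be hard to recover later.
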